### Interventions

All patients will receive conventional rehabilitation, which includes joint loosening training, passive stretching, relaxation training, stepping training, and endurance training, whereas the VR group will receive 30 min of conventional rehabilitation and 30 min of VR training. The control group will receive 30 min of conventional rehabilitation and 30 min of upper extremity function exercise. Rehabilitation will be done five times per week for 4 weeks in separate rooms for a total of 20 sessions in the hospital. All treatments will be performed by licensed therapists with at least 3 years of practice experience. The interventions of the two groups are as follows.

### Interventions group

VR training and conventional rehabilitation will be used in the intervention group for 30 min. The VR system hardware is mainly composed of the following four parts: Wii host, remote controller (RC), complementary metal oxide semiconductor (CMOS) infrared sensor, and liquid crystal display (LCD). The RC uses embedded acceleration sensors to detect the direction, speed, and acceleration of the user's upper extremities and hands in three-dimensional space. CMOS infrared sensors capture and reproduce the patient's motion trajectory on a display by receiving infrared signals from both ends of the receiving optical sensor rod. Training programs include tennis, table tennis, and kitchen cooking. Upper extremity movements include shoulder flexion, stretching (tennis), shoulder internal rotation, external rotation (tennis); elbow flexion, stretching (tennis, table tennis, and kitchen cooking); and radial joints before and after rotation (tennis, table tennis, and kitchen cooking). During Wii game training, the patient will stay seated and use the affected upper extremity for game training, and if the patient is unable to hold the remote controller, an elastic bandage is used to fix the controller on the affected upper hand. The existing evidence on rehabilitation of the upper extremity after stroke proposes that constraining or forced use of 90% of the training time is devoted to using the non-paretic upper extremity with a mitt to encourage the use of the more affected extremity (24). Taking into account the previous level of stroke patients, the degree of the Wii training difficulty will be divided into several degrees in all courses. To prevent weariness during training, the therapist will give the participants a thorough explanation of the Wii game training procedure.

### Control group

Control group participants will receive conventional rehabilitation training and upper extremity function exercises. Upper extremity function exercises include passive and active assistance, active training of the upper extremities on the affected side, training in pushing scrub boards on the upper extremities on the affected side, training in grasping and opening the upper extremities on the affected side, training of a range of motion, muscle strength, sitting balance ability with the help of tools, such as scrub boards, rollers, and sticks, using screws, and other training of hand fine movements, and sitting balance ability using tools such as a chair.

### Sample size

The objective of this study is to explore VR and conventional rehabilitation for upper extremity motor function after a stroke and to calculate the sample size by using G-Power (version 3.1) software. The effect size f is expected to be at least 0.25, and since the power is 0.80, the protocol should include 65 participants. Considering an expected 15% dropout rate, the sample size is increased to 78 participants.

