## Methods and analysis

### Design and setting

This is a prospective, randomized controlled trial conducted by the Second Hospital of Jiaxing. A total of 78 patients who meet the inclusion and exclusion criteria will be randomly divided into two groups. The intervention group will receive VR training and conventional rehabilitation treatment, and the control group will receive conventional rehabilitation treatment only. All treatments will be provided five times per week for 4 weeks. The primary outcome is the degree of restored upper extremity motor function, which is evaluated by the Fugl-Meyer Assessment Upper Extremity Scale (FMA-UE). Secondary outcomes are neuroimaging outcomes, which are measured by resting-state functional magnetic resonance imaging (rs-fMRI), task-state functional magnetic resonance imaging (ts-fMRI), and electroencephalography (EEG). All outcomes will be evaluated at baseline and weeks 4 and 8. The study's flow chart is shown in Figure 1. The Standard Protocol Items: Recommendations for Interventional Trials (SPIRIT) checklist (23) is detailed in an additional document available upon request (Supplementary material), and the schedule of this study is shown in Table 1.

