### Data analysis

Data analysis will be performed using SPSS software (IBM, Statistics 25 version). Measurement data that follow a normal distribution as a whole will be expressed as mean ± standard deviation (X ± SD), and the whole data will not follow a normal distribution in median (interlude spacing) [M(P25–P75)]. The count data will be expressed as the number of cases (composition ratio) [*N*, (%)], and the analysis is tested by the *X*^2^ or Fisher's exact tests precisely. The comparison between the groups will be carried out by the *t*-test or the Mann–Whitney *U*-test based on whether the measurement data present a normal distribution and homogeneous variance to compare the differences in FMA-UE and independent sample *t*-test for the parameter in FIM, BI, grip strength, fMRI and EEG at a *p*-value below 0.05. There are no interim analyses planned.

fMRI image processing will use the statistical parameter graph software statistical parametric mapping (SPM)12. Before data processing, all data will be adjusted in orientation; and then head-action alignment, high-resolution structural image, and the average functional image will be registered; the high-resolution structural image after registration will be split; all the aligned functional images will be standardized to the Montreal Neurological Institute space using the standardized parameters generated during the segmentation process; the standardized voxel size is 3 mm × 3 mm × 3 mm; and the standardized functional image is spatially smoothed. Through an intragroup analysis, a paired *t*-test will be performed to assess brain alterations in each group (before and after the treatment). Age and gender will be taken into account as variables in the data analysis. The association between the improvement value of the correlation scales and the change in fMRI image data will be examined using the Pearson correlation coefficient.

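### The 80% power stated for f = 0.25 with 65 participants does not follow from the planned two-group test; on the usual reading of f (d = 0.50) the power is about 51%

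*Protocol article*

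**What the plan says.** The Sample size section names the software ("calculate the sample size by using G-Power (version 3.1) software") and then states: "The effect size f is expected to be at least 0.25, and since the power is 0.80, the protocol should include 65 participants". It goes on: "Considering an expected 15% dropout rate, the sample size is increased to 78 participants". It gives no test family, number of measurements or correlation.

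Design and setting says that patients "will be randomly divided into two groups", with assessments at baseline, week 4 and week 8. The Abstract names change in FMA-UE as the primary outcome.

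Data analysis gives the only between-group analysis of that outcome: "The comparison between the groups will be carried out by the *t*-test or the Mann–Whitney *U*-test", the choice being "based on whether the measurement data present a normal distribution and homogeneous variance to compare the differences in FMA-UE". The significance level there is 0.05, with sidedness not stated. The article describes no repeated-measures ANOVA and no baseline-adjusted analysis of FMA-UE. Age and gender are mentioned only in the fMRI paragraph.

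**The concern.** Cohen's f belongs to the analysis-of-variance family. With two groups of equal size it converts to a standardised mean difference by d = 2f, so f = 0.25 is d = 0.50. A two-sample t-test at that effect needs about twice 65 patients for 80% power. The stated effect, power, sample size and test therefore cannot all hold under the ordinary meaning of f.

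FMA-UE is the sole primary outcome, and no interim look is planned at which the size could be revisited. If the ordinary meaning was intended, a non-significant result would be about as likely as a significant one even with the assumed effect present. Readers would nevertheless take it as coming from a trial with 80% power. If another meaning was intended, the effect the trial is sized for is larger than the paragraph suggests.

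**Working it through.** **Inputs.** From Sample size: f = 0.25, power 0.80, N = 65 evaluable, 15% dropout, 78 enrolled. From Design and setting: two groups. From Data analysis: t-test or Mann-Whitney test at 0.05. Assumed: two-sided (one-sided also shown) and 1:1 allocation, so 32 and 33.

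**1. Where 65 comes from.** In a two-group repeated-measures F-test with m measurements and common correlation ρ, the noncentrality is
- interaction (shown here for m = 2): λ = N f² m / (1 − ρ)
- between-group: λ = N f² m / (1 + (m − 1)ρ)

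With m = 2 and ρ = 0, λ = 65 × 0.0625 × 2 = 8.125 on (1, 63) degrees of freedom, and power is 0.801. With 64 patients it is 0.795, so 65 is the smallest N. The between-group test over m = 3 visits at ρ = 0.25 gives the same λ, since 3/(1 + 2 × 0.25) = 2, and so also gives 65.

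The number moves a good deal with these settings. With three measurements, the N needed is:

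| Correlation | Between-group test | Interaction test |
|---|---|---|
| 0 | 44 | 53 |
| 0.5 | 86 | 28 |

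**2. Dropout.** 65/0.85 = 76.5, so 77; 66/0.85 = 77.6, so 78. With 33 per arm the stated 78 is in order.

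**3. The planned test, f read as the two-group effect.** d = 2 × 0.25 = 0.50. The noncentrality is d√(n₁n₂/(n₁+n₂)) = 0.50 × √(32 × 33/65) = 2.015, against a critical value of 1.998 on 63 degrees of freedom.

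| Evaluable | Two-sided | One-sided |
|---|---|---|
| 65 (32/33) | 0.510 | 0.636 |
| 78 (39/39) | 0.587 | 0.707 |
| 128 (64/64) | 0.801 | 0.879 |

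The Mann-Whitney test at 65, with relative efficiency 0.955 for normal data, gives about 0.49. For 80% power two-sided, 128 evaluable patients are needed (128/0.85 = 150.6, so 151 enrolled). With 65, the difference detectable at 80% power is d = 0.706, so f = 0.35; with 78 it is d = 0.643.

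**4. The planned test, f read as the two-measurement interaction.** A t-test on change is equivalent to that F-test. Setting d²N/4 equal to λ = 2Nf² gives d = √(8 × 0.0625) = 0.707 in SDs of the change score, and power with 32/33 is 0.801. At ρ = 0 the SD of change is √2 times the raw-score SD, so the difference is 0.707 × √2 = 1.0 raw-score SD.

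**5. d = 0.50 in raw-score SDs, change analysed.** The SD of change is the raw SD times √(2(1 − r)), with r the correlation between baseline and follow-up scores. The effect on change is therefore 0.50/√(2(1 − r)):

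| r (assumed) | Effect on change | Power, 65 evaluable |
|---|---|---|
| 0.5 | 0.50 | 0.51 |
| 0.6 | 0.56 | 0.60 |
| 0.7 | 0.65 | 0.73 |
| 0.75 | 0.71 | 0.80 |
| 0.8 | 0.79 | 0.88 |

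**The case against.** The strongest defence is that the paragraph never says f is a one-way two-group effect. Since 65 is exactly what a two-measurement interaction at zero correlation gives, that may be what was computed. The primary outcome is change, and a t-test on change is the same test as that interaction, so on this reading the planned analysis does deliver 80%. Step 5 adds a second route: an effect of 0.50 raw-score SDs with a correlation of about 0.75 also reaches 80%.

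This much stands. A reader might infer that the trial simply has 51% power, or that a repeated-measures calculation has nothing to do with the planned test. The article supports neither inference: 51% depends on how f is read, and the equivalence with a t-test on change is real.

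It does not rescue the paragraph. Each route to 80% needs a setting the article does not state. The interaction route uses two measurements where the trial has three. It also assumes zero correlation between repeated FMA-UE scores in the same patient, which is implausible, and it makes the assumed effect 0.71 SD of the change score rather than 0.50.

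It can also be said that a condensed article leaves such settings to the full protocol or the SAP, neither of which is shown. That is fair for the omissions alone. The point here is different: a specific power claim and a specific test, both printed in the article, do not agree on the ordinary meaning of the effect size.

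**Conclusion.** The concern holds in conditional form. The claim of 80% power for f = 0.25 with 65 participants does not follow from the planned t-test or Mann-Whitney test.

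- If f carries its usual two-group meaning, power is about 51% (two-sided 5%, 1:1 allocation). Neither a one-sided test nor full retention of all 78, nor both together (71%), reaches 80%.
- If f was an interaction effect over two uncorrelated measurements, the power is right. The effect is then 0.71 SD of change, or one full raw-score SD.
- If d = 0.50 is in raw-score SDs and change is tested, power runs from 0.51 to 0.88 for assumed correlations from 0.5 to 0.8.

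The article does not show which reading was used, so no single power figure can be called the trial's true power. What can be said without knowing it is that 65 evaluable patients give 80% power for a difference of about 0.71 SD of whatever variable the t-test is applied to.

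**What to change.** Keep 78 patients and restate the Sample size paragraph for the test actually used. For example:

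> With 65 evaluable patients, two-sided alpha 0.05 and a two-sample t-test on change in FMA-UE, the trial has 80% power to detect a difference of 0.71 SD of the change score (f = 0.35); power for 0.50 SD (f = 0.25) is 51%.

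If the original calculation was a repeated-measures one, say so, with the number of measurements and the correlation, and express the effect on the scale of the planned test.

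This costs one reworded paragraph and no extra patients. The stated power or detectable effect becomes less favourable.

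A further option is to make baseline-adjusted ANCOVA the primary analysis. For d = 0.50 in raw-score SDs, with noncentrality N f²/(1 − r²), its power with 65 patients is 0.63, 0.70, 0.79 and 0.91 at r = 0.5, 0.6, 0.7 and 0.8. This changes the primary analysis and is not a rewording, so it would have to be amended before the data are seen. The article gives no value for r, so any value used must be labelled an assumption. Correcting the paragraph does not depend on this option.

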### Outcome measures

Participants will be evaluated at baseline and weeks 4 and 8. All evaluations will be conducted by researchers who will be blinded to the treatment allocation.

### Primary outcome

The primary outcome is the FMA-UE, which has been developed as an evaluative measure of the upper limb functionality recovery poststroke (25–27). The FMA-UE score is 66 points, with lower scores indicating more severely impaired UE and higher scores indicating better motor function improvements. The baseline assessment results of this study are recorded as FM0, the second assessment results are carried out as FM1 after interventions, and the follow-up assessment results are recorded as FM2.

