**Methods/design:**

In this single-center, randomized, parallel-group clinical trial with a blinded assessment of outcomes, a total of 78 stroke patients will be assigned randomly to either the VR group or the control group. All stroke patients who have upper extremity motor deficits will be tested with functional magnetic resonance imaging (fMRI), electroencephalography (EEG), and clinical evaluation. Clinical assessment and fMRI will be performed three times on each subject. The primary outcome is the change in performance on the Fugl-Meyer Assessment Upper Extremity Scale (FMA-UE). Secondary outcomes are functional independence measure (FIM), Barthel Index (BI), grip strength, and changes in the blood oxygenation level-dependent (BOLD) effect in the ipsilesional and contralesional primary motor cortex (M1) on the left and right hemispheres assessed with resting-state fMRI (rs-fMRI), task-state fMRI (ts-fMRI), and changes in EEG at the baseline and weeks 4 and 8.

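### The primary outcome has no named time point: FMA-UE is measured at weeks 4 and 8, and the plan does not say which visit the primary test uses

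*Protocol article*

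**What the plan says.** The protocol article defines the primary outcome in three places, none with a visit:

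- Abstract, Methods/design: "The primary outcome is the change in performance on the Fugl-Meyer Assessment Upper Extremity Scale (FMA-UE").
- Design and setting: "The primary outcome is the degree of restored upper extremity motor function, which is evaluated by the Fugl-Meyer Assessment Upper Extremity Scale (FMA-UE").
- Primary outcome: the FMA-UE is named and its three recordings are labelled. Baseline is FM0; then "the second assessment results are carried out as FM1 after interventions, and the follow-up assessment results are recorded as FM2".

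The schedule is the same for every endpoint: "All outcomes will be evaluated at baseline and weeks 4 and 8". Table 1 agrees, with FMA-UE ticked at baseline, at the 4-week treatment column and at the 8-week follow-up column.

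The Data analysis section gives the between-group test as a t-test or Mann-Whitney U-test, chosen by "whether the measurement data present a normal distribution and homogeneous variance to compare the differences in FMA-UE". The threshold, shared with the secondary endpoints, is "at a *p*-value below 0.05". It also says: "There are no interim analyses planned". The section gives no primary visit, order of testing, split of alpha, requirement that both visits succeed, or joint model over visits for FMA-UE.

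**The concern.** The planned test compares two groups on one value per patient. With two post-baseline values available, it must be run either at one visit, chosen by a rule the text does not give, or at each visit. A null result at one visit and p = 0.04 at the other could then be reported as a positive primary outcome without departing from the written plan. The 5% error rate would not hold for that claim, and a reader of the final report could not tell from the protocol which result had been intended as primary.

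**Working it through.** **1. The plan's own figures, and whether they settle the visit.** The threshold is 0.05 per test. Sidedness is not stated; two-sided is assumed here. The Sample size section says: "The effect size f is expected to be at least 0.25, and since the power is 0.80, the protocol should include 65 participants". It names no visit, test family, number of measurements or correlation. The figure 65 comes out of a repeated-measures ANOVA with f = 0.25, 2 measurements and correlation 0 (power 0.8014 at N = 65). Those settings are a reconstruction and do not identify a visit. For dropout, 65/0.85 = 76.5, so 77, and 66/0.85 = 77.6, so 78; the enrolled number of 78 is consistent with an even evaluable number. The sample size therefore does not answer the question. Whether it suits the planned test is a separate matter.

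**2. One visit named.** One test at two-sided 0.05 has a false-positive rate of 0.05.

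**3. Both visits tested, either sufficient (a reading left open, not stated).** Let Z1 and Z2 be the week 4 and week 8 test statistics under no effect, with correlation r. Then

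false-positive rate = 1 − P(|Z1| < 1.96 and |Z2| < 1.96).

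For r = 0 this is 1 − 0.95² = 0.0975, the upper end. For r > 0 it comes from the bivariate normal distribution. The documents give no value for r, so a range is assumed. The last column applies Bonferroni, 0.025 per visit.

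| r (assumed) | Either visit at 0.05 | Either visit at 0.025 |
|---|---|---|
| 0 | 0.0975 | 0.0494 |
| 0.5 | 0.0907 | 0.0465 |
| 0.7 | 0.0835 | 0.0430 |
| 0.8 | 0.0781 | 0.0402 |
| 0.9 | 0.0704 | 0.0362 |
| 1 | 0.05 | 0.025 |

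Simulated t-tests with 33 per arm gave 0.094, 0.082 and 0.070 at r = 0.5, 0.7 and 0.9, in line with the formula. Counting only results in favour of VR, the nominal 0.025 becomes 0.0454 at r = 0.5 and 0.0352 at r = 0.9.

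**4. Why 0.5 belongs in the range.** If the endpoint is change from baseline, FM1 − FM0 and FM2 − FM0 share FM0. Assume equal variance s² at the three visits and a common correlation c between them. The covariance of the two changes is s²(c − c − c + 1) = s²(1 − c), and each variance is 2s²(1 − c). Their correlation is therefore 0.5 whatever c is, and the rate is 0.0907.

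**5. After the fix.** With one named visit, or week 8 tested only if week 4 is significant, the rate is at most 0.05 for every r.

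**The case against.** The strongest reply is that measuring at two visits is not the same as testing at two visits. No section says that a test is run at each visit, or that success at either is enough; the 0.05 in Data analysis is a general significance threshold and not a success rule. This stands. A reader might infer that the trial does test its primary outcome twice and does have a false-positive rate above 5%. The documents do not support that flat statement, only the conditional one.

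A reader might also infer that raw score and change are rival primary endpoints, which would multiply the tests further. This is weak. The Abstract, and Design and setting with its wording about restored function, both point to change. The Primary outcome section describes the instrument and labels its recordings without saying that raw scores are analysed.

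The text also leans towards week 4: treatment lasts 4 weeks, FM1 is the post-intervention value, and FM2 and the week 8 column are labelled follow-up. That is a hint and not a designation.

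The aim is worded as exploratory, but the article names a primary outcome and powers the trial, so the question of what counts as the primary result remains. The absence of interim analyses does not help, because the two visits are two endpoints and not interim looks.

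Finally, testing order and covariate adjustment can reasonably be left to a statistical analysis plan. The time point is different: it is part of the definition of the primary outcome, which this article states three times.

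**Conclusion.** The point holds in conditional form. The primary outcome is defined without a time point, and the planned single-time-point test does not say which FMA-UE difference it uses. If both visits were tested at 0.05 and either could be claimed, the false-positive rate would be about 7% to 9%, that is 1.4 to 1.8 times the nominal level (0.0704/0.05 and 0.0907/0.05). This rests on two things the documents do not give: an either-visit rule, which they leave open, and a correlation of 0.9 down to 0.5 between the test statistics, which is assumed. Two-sided testing is assumed as well. The missing time point itself rests on no assumption.

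**What to change.** Before outcome data are seen, name one primary endpoint. One example is the between-arm difference in FMA-UE at week 4 (FM1), adjusted for FM0 by ANCOVA, at two-sided 0.05. This also uses the baseline value already collected, which the unadjusted two-group test of follow-up scores or simple changes does not use as a covariate. Make week 8 (FM2) a secondary endpoint, tested only if week 4 is significant. Align the Abstract, Design and setting, Primary outcome and Data analysis sections so that all four give the same variable, visit and test.

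If the sponsor prefers to keep both visits as primary with either sufficient, 0.025 per visit holds the rate at or below 0.05, at the price of power at each visit.

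The recommended change costs wording only, with no new visits, patients or procedures. Its downside is that an effect seen only at week 8 could not be claimed as the primary result.
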